## Abstract

**Background:**

IBS affects 10-22% of the UK population. Abdominal pain, bloating and altered bowel habit affect quality of life, social functioning and time off work. Current GP treatment relies on a positive diagnosis, reassurance, lifestyle advice and drug therapies, but many suffer ongoing symptoms.

A recent Cochrane review highlighted the lack of research evidence for IBS drugs. Neither GPs, nor patients have good evidence to inform prescribing decisions. However, IBS drugs are widely used: In 2005 the NHS costs were nearly £10 million for mebeverine and over £8 million for fibre-based bulking agents. CBT and self-management can be helpful, but poor availability in the NHS restricts their use. We have developed a web-based CBT self-management programme, Regul8, based on an existing evidence based self-management manual and in partnership with patients. This could increase access with minimal increased costs.

**Methods/Design:**

The aim is to undertake a feasibility factorial RCT to assess the effectiveness of the commonly prescribed medications in UK general practice for IBS: mebeverine (anti-spasmodic) and methylcellulose (bulking-agent) and Regul8, the CBT based self-management website.

135 patients aged 16 to 60 years with IBS symptoms fulfilling Rome III criteria, recruited via GP practices, will be randomised to 1 of 3 levels of the drug condition: mebeverine, methylcellulose or placebo for 6 weeks and to 1 of 3 levels of the website condition, Regul8 with a nurse telephone session and email support, Regul8 with minimal email support, or no website, thus creating 9 groups.

Outcomes: Irritable bowel symptom severity scale and IBS-QOL will be measured at baseline, 6 and 12 weeks as the primary outcomes. An intention to treat analysis will be undertaken by ANCOVA for a factorial trial.

**Discussion:**

This pilot will provide valuable information for a larger trial. Determining the effectiveness of commonly used drug treatments will help patients and doctors make informed treatment decisions regarding drug management of IBS symptoms, enabling better targeting of treatment. A web-based self-management CBT programme for IBS developed in partnership with patients has the potential to benefit large numbers of patients with low cost to the NHS. Assessment of the amount of email or therapist support required for the website will enable economic analysis to be undertaken.

**Trial Registration:**

ClinicalTrials.gov Identifier (NCT number): NCT00934973.

## Background

Irritable bowel syndrome (IBS) is a common chronic gastrointestinal disorder that affects 10 - 22% of the UK population and costs the National Health Service (NHS) over 200 million pounds a year [1,2]. Abdominal pain, bloating and altered bowel habit affect quality of life, social functioning and time off work [3,4]. Treatment relies on a positive diagnosis, reassurance, lifestyle advice, and drug and psychological therapies. However, many patients suffer ongoing symptoms. Drug treatment includes: anti-spasmodics, dietary fibre/bulking agents, antidepressants and anti-diarrhoeals. Bulking agents and antispasmodics and are the most commonly prescribed medications in the UK and Europe. Newer '5HT' antagonist drugs, such as alosetron, have been developed over recent years and used in the U.S.A. but have been hampered by problematic side effects such as ischaemic colitis and severe constipation[5] and are not licenced in the UK. There is a significant psychological aspect to IBS in many patients and psychological therapies, CBT, biofeedback and hypnotherapy can help[6], but availability of these treatments is limited.

Web-based CBT has been shown to be helpful for other conditions e.g. depression[13] and tinnitus[14]. Thus this could be an efficient, cost effective way of providing help to those with IBS. Despite extensive literature searching before the start of the study, we found no published evaluations of computer-based CBT programmes for IBS. The Gut Trust (formerly called the IBS network) (a patient self-help group) provides an on-line self-management programme (at a charge) but this is not CBT-based and has not been critically evaluated in a trial. NICE has recently recommended the use of Computer CBT for depression, panic and phobia in Primary Care[15]. Development and testing of a computerised CBT programme for IBS has the potential to make CBT more widely available for IBS without increased costs. The increasing availability of the internet makes this a good medium to provide easily accessible patient information and self-management programmes. The majority of households in the UK have internet access (Office for National Statistics August 2009) with figures increasing each year currently 70% have access and this an increase of 11% on the previous year.

### Background to the Project

Over the last year we developed a web-based CBT self-management programme for IBS based on a paper-based manual[16] that was originally developed and tested by one of our team in a RCT of 70 patients in primary care ([name]) [17]. As each module was developed think aloud[18] interviews were undertaken with four patients with IBS whilst they worked through the programme to ensure that the website addressed issues important to people with IBS and was relevant, understandable, navigable and user friendly. The interviews were transcribed verbatim and the feedback was used to modify the site as it was developed.

The website was created using the LifeGuide software [19], which allows people without a programming background to create web-delivered interactive interventions. The web-based intervention we developed consists of 8 sessions for participants to work through over 6 weeks (see table 1 for an overview of each session) and includes interactive components such as: the development of a personal model, creating symptom diaries, goal sheets and thought records. Interactive components help users to remember advice and reflect and provide a "substitute" for the therapist and personalises programme to user [19] This enables users to focus on personally relevant aspects of the programme. Early in each session participants review key points from the previous session and review participant homework. The website includes a 'My Tasks' Section that records participant previous answers and homework.

**Table 1 T1:** Summary of the Regul8 Web-Based Self-Management Sessions

Session 1: Understanding your IBS	Rationale for self-management which includes the following explanations: 1. Possible causes of IBS and illustrative physiology of the digestive system together with the functional changes that occur in the gut as a result of IBS. 2. How the autonomic nervous system ("fight-or-flight" stress system) may interact with the enteric nervous system
**Session 2:** Assessing your symptoms	Self-assessment of the interaction between thoughts, feeling and behaviours and how these can impact on stress levels and gut symptoms. Development of a personal model of IBS which incorporates these elements. Homework: Daily diaries of the severity and experience of IBS symptoms in conjunction with stress levels and eating routines/behaviours

**Session 3**. Managing Symptoms and Eating	Review of the symptom diary Behavioural management of the symptoms of diarrhoea and constipation, and common myths in this area are discussed. Goal setting is explained. The importance of healthy, regular eating and not being overly focused on elimination is covered. Homework: Goal setting for managing symptoms and regular/healthy eating. Goal setting, monitoring and evaluation continue weekly throughout the programme.

**Session 4**. Exercise and Activity	Importance of exercise in symptom management is covered Identifying activity patterns such as resting too much in response to symptoms or an all-or-nothing style of activity is addressed. Homework: Goal setting for regular exercise and managing unhelpful activity patterns if relevant.

**Session 5**. Identifying your thought patterns	Identifying unhelpful thought (negative automatic thoughts) in relation to high personal expectations and IBS symptoms is introduced. Link between these thoughts, feelings, behaviours and symptoms is reinforced. Homework: Goal setting plus daily thought records of unhelpful thoughts related to personal expectations and patterns of over activity.

**Session 6**. Alternative thoughts	The steps for coming up with alternatives to unhelpful thoughts are covered together with personal examples. Homework: Goal setting plus daily thought records including coming up with realistic alternative thoughts.

**Session 7**. Managing Stress and Sleep	Basic stress management and sleep hygiene are discussed. Diaphragmatic breathing, progressive muscle relaxation and guided imagery relaxation are presented in video and audio formats. Homework: Goal setting for stress management, relaxation techniques and good sleep habits.

**Session 8**. Managing flare-ups and the future	The probability of flare-ups is discussed and patients are encouraged to develop achievable, long term goals and to continue to employ the skills they have learnt throughout the manual to manage flare-ups and ongoing symptoms.

### Aims

To pilot a factorial RCT to assess the effectiveness of the prescribed medications in UK general practice for IBS: mebeverine (an anti-spasmodic) and methylcellulose (bulking-agent) against placebo and Regul8, a CBT based self-management website for IBS developed specifically for this study.

The pilot will provide information for a definitive trial and all the trial procedures will be tested. The results of the pilot will enable decisions to be made regarding the full trial. For example:

1) Is it appropriate to test a fibre-based bulking agent in all groups of IBS patient (i.e. in those with diarrhoea symptoms and alternating symptoms as well as those with constipation symptoms)? Most guidelines advocate bulking agents for those with constipation symptoms to increase stool weight and accelerate gut transit [3,11]. The position in those with alternating or diarrhoea symptoms is less certain - increasing stool bulk may stabilise bowel habit and reduce pain or may exacerbate loose stools - trials have tested bulking agents in IBS patients with all 3 patterns of bowel habit and symptom exacerbation seems rare [4,8,20,21]. However, if the results of the pilot show that methylcellulose may significantly worsens symptoms in those with diarrhoea then this group will not be randomised to methylcellulose in the full trial.

2) Should the full trial test the website with minimal email support on request or with the scheduled telephone nurse consultation after session two plus the minimal email support?

## Methods/Design

### Design

Placebo controlled randomised controlled trial with a 3 (drug) × 3 (self-management website) factorial design

### Participants

Inclusion criteria are patients aged 16 to 60 years presenting to general practice with symptoms of IBS that fulfil the Rome III criteria (maximum age 60 years as NICE guidelines advise that a new change in bowel habit in over 60 year olds should have further investigations[11])

### Exclusion criteria

Atypical symptoms - (unexplained weight loss, rectal bleeding), diagnosis of inflammatory bowel disease, Coeliac disease or peptic ulcer disease, pregnant or breast feeding, currently taking or allergy to mebeverine or methylcellulose. If patients are already taking mebeverine or methlycellulose but are keen to enter the trial they will be able to do so if they fulfil the inclusion criteria, do not meet any of the other exclusion criteria and they undertake a 4 week mebeverine and methylcellulose free wash out period before entering the trial.

### Withdrawal criteria

Participants will be withdrawn from the trial if there are any safety concerns regarding continuing the trial medication, if there are any concerns regarding informed consent or if the participant chooses to withdraw.

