### Intervention

135 patients will be randomised to: mebeverine (135 mg three times a day), methylcellulose (3 tablets twice a day), or a placebo tablet for 6 weeks. To ensure double blinding, all participants will take three over-encapsulated identical tablets in the morning, one at lunchtime and three at teatime.

They will also be randomised to 1 of 3 website conditions: access to Regul8 with a 30-45 minute nurse telephone session after session 2 (to encourage engagement with the CBT programme) and email support on request, the website with minimal support (i.e. technical email support on request), or no website, thus creating 9 groups.

There will be double-blinding for medication groups, single-blinding for the website (participants will not be able to be blind to website access). Website access will be with a personal password so that usage can be assessed. All patients will receive a telephone call in the first week to check they have no problems with the medication or paperwork. Those not randomised to website access will receive standard patient information and will be offered access to the website at the end of the trial.

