### Data collection

Participant data will be collected on the MIBS trial website. Baseline data will be collected from included patients before randomisation and will be co-ordinated by the trial manager who will be blind to treatment allocation. All baseline and outcome data is patient self-completed away from the study team, thus avoiding any influence of the study team on the responses and reducing bias. Participants will be given a unique password to log onto the website. Their data will be identified by a unique identification number and will be kept separate from any personal identifying data to maintain confidentiality.

An on-line baseline assessment which includes socio-demographic details and the measures detailed below will be completed by all participants prior to the nurse visit and before randomisation. These are well-recognised, validated measures that are widely used and will enable us to gain a clear picture of participants IBS and the impact it has on their lives.

Those randomised to the self management programme will complete on-line symptom severity questions, symptom, food and exercise diaries, questions about stress and triggers and their symptoms and their coping strategies. These data will be collected and stored and may be used to provide information to assess the self management programme but will mostly be used by the participants themselves to monitor their progress and inform themselves about their own symptoms, triggers and coping strategies as part of the cognitive behavioural therapy based self-management programme.

Outcome data and questionnaires outlined below will be completed at 6 and 12 weeks post randomisation by all participants. Participants will be sent a reminder email at 6 and 12 weeks to prompt them to complete the questionnaires. If it has not been completed within one week of the reminder, a further reminder will be sent. One week after that, if no data has been entered, the research nurse will ring the participant to ask if she can collect the data over the telephone.

The patients GP notes will be reviewed at 12 weeks to assess the number of GP contacts in the year prior to entering the study and in the 3 months since the study. In a full trial a one year notes review is planned. Other studies have shown an impact on GP contacts from patient self management programmes[22].

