### Primary Outcome measures

Change in the Irritable Bowel Symptom Severity Scale (IBS SSS score) and IBS Quality of Life Questionnaire (IBS-QOL) from baseline to 12 weeks.

The IBS SSS [23] is a 5 item self-administered questionnaire measuring: severity of abdominal pain, duration of abdominal pain, abdominal distension/tightness, bowel habit, quality of life. Maximum score 500: < 75 normal bowel function, 75-174 mild IBS, 175-299 moderate IBS, 300-500 severe IBS). The IBS-QOL[24] is an extensively validated quality of life measure for IBS: 34 items, 8 subscales, item responses graded on a 5 point scale, total score 0-100 with higher scores indicating better health related QOL. Administered at baseline and 6 weeks (end of treatment) and12 weeks (6 months and 12 months would also be planned for the full trial).

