### Analysis

An intention-to-treat analysis, of change in the IBS SSS and IBS-QOL at baseline, 6 weeks and 12 weeks (6 mnth and 1 yr are planned for the full trial) will be undertaken by ANCOVA for a factorial trial. In the main trial (but not in the pilot): subgroup analysis will be performed using regression modelling to determine if symptoms subgroup (diarrhoea-predominate, constipation-predominate and alternating symptoms) predicts differences in outcome. Other potential factors that may affect outcome will be explored: severity of presenting symptoms, duration of presenting symptoms, age and sex.

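### A medication safety concern takes a participant out of the whole factorial trial, although it bears on only one of the two randomised factors

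*Protocol article*

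**What the plan says.** The section on withdrawal criteria is the article's only withdrawal rule: "Participants will be withdrawn from the trial if there are any safety concerns regarding continuing the trial medication". The same sentence attaches the same consequence to doubts about informed consent and to the participant's own choice. It does not distinguish stopping the capsules from leaving the study.

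Other sections bear on this:

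- **Design and Intervention.** The trial is a 3 (drug) × 3 (website) factorial. After the drug allocation, "They will also be randomised to 1 of 3 website conditions". Drug treatment is mebeverine, methylcellulose "or a placebo tablet for 6 weeks".
- **Primary Outcome measures.** The endpoint is change in IBS SSS and in "IBS Quality of Life Questionnaire (IBS-QOL) from baseline to 12 weeks".
- **Data collection.** Questionnaires "will be completed at 6 and 12 weeks post randomisation by all participants", online and with email reminders. If nothing arrives, "the research nurse will ring the participant to ask if she can collect the data over the telephone". In addition, "The patients GP notes will be reviewed at 12 weeks to assess the number of GP contacts".
- **Analysis.** The plan is "An intention-to-treat analysis, of change in the IBS SSS and IBS-QOL" by factorial ANCOVA.
- **Discussion.** Recruitment and drop-out rates and the acceptability of the medication are among the things the pilot is to find out.

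**The concern.** A safety concern about a capsule is a reason to stop the capsule. It gives no reason to stop a CBT website or to stop asking for questionnaires. As worded, the rule ends participation in both factors for a reason that belongs to one.

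Three things are at stake. First, a participant with website access may lose it part-way, which dilutes the website comparison. Second, the 6- and 12-week outcomes may not be obtained although the participant is willing to give them. These gaps may differ by drug arm: the Aims section itself asks whether methylcellulose makes symptoms worse in patients with diarrhoea. Third, one count then covers both stopping the drug and leaving the study. The definitive trial needs these separately, because the first describes tolerability and the second drives the sample size.

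**Working it through.** **Does outcome collection depend on dosing?** Drug is given for 6 weeks and the primary endpoint is at 12 weeks, so by design every participant is off trial drug for the second half of follow-up. Online questionnaires, the telephone back-up and the notes review need no drug intake. Nothing in data collection therefore requires a participant who stops the drug to leave.

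**Does another section supply a milder rule?** The nearest is the provision under Study Procedures that lets participants open capsules so that they can remain in the trial. It covers difficulty in swallowing only. No section says that a participant stopped for drug safety keeps the website or is still followed up.

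**The plan's own sample size.** Inputs from the Sample size section: difference 53, SD 80, 80% power, 95% confidence (read as two-sided 5%), 20% drop-out, 135 recruited.

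- n per group = 2(1.960 + 0.842)² × 80² / 53² = 35.8, so 36; the plan states 35.
- Total = 3 × 35 / 0.8 = 131.25, so 132; the plan states 130.

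Both are close enough to count as reproduced. The planned number is not at issue here.

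**How many participants could be affected?** The document gives no safety-stop rate. Assume a share s between 1% and 10%.

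- All participants: 135 × s = 1.35 to 13.5, about 1 to 14.
- With website access (two of three conditions, 90 participants): 90 × s = 0.9 to 9, about 1 to 9.

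**Power.** Each level of a factor has 135 / 3 = 45 participants. The calculation is a two-sided t-test at 5% (noncentral t), difference 53, SD 80. If the stops are part of the 20% allowance, n = 45 × 0.80 = 36. In the worst case all are added to it, n = 45 × (0.80 − s), and every stopped participant would otherwise have completed follow-up.

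| Case | n per level | Power |
|---|---|---|
| Stops within the 20% | 36 | 79.2% |
| s = 1% on top | 35.55 | 78.6% |
| s = 5% on top | 33.75 | 76.5% |
| s = 10% on top | 31.5 | 73.5% |

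The normal approximation gives 80.3% at n = 36.

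**Effect of ANCOVA.** Adjusting for baseline with correlation ρ reduces the SD to 80 × √(1 − ρ²). The document does not give ρ, so a range is assumed.

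| ρ (assumed) | Power, n = 36 | Power, n = 31.5 | Fall (points) |
|---|---|---|---|
| 0 (unadjusted) | 79.2% | 73.5% | 5.7 |
| 0.3 | 82.8% | 77.4% | 5.4 |
| 0.4 | 85.6% | 80.6% | 5.0 |
| 0.5 | 89.3% | 84.8% | 4.5 |

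**The case against.** The best defence is that the harm is inferred. The rule does not say that website access ends, that questionnaires stop or that the notes review is cancelled. Such detail is commonly left to a full protocol, which is not shown. Outcomes from all participants, the reminders, the telephone back-up and the capsule-opening provision all point to an intention to retain people. Safety stops may also be few: the exposure is 6 weeks to widely used drugs, allergy to either drug is an exclusion, and the Aims section describes symptom exacerbation on bulking agents as seemingly rare. The trial is a pilot that does not claim power for a definitive effect.

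Much of this limits the size of the point. The stop rate is an assumption, the power loss may be nil, and the unadjusted figures are pessimistic for an ANCOVA.

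The wording itself still stands. The point rests on a consequence the article states, not on a detail it omits. Listing it with consent problems and participant choice suggests leaving the study rather than stopping a drug, and no other section corrects that reading.

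A reader might go further and infer that the rule contradicts intention to treat, or that collected data are discarded. The document supports neither. The rule removes no one from the analysis and says nothing about deleting data. It leaves outcomes missing that an intention-to-treat analysis needs, which weakens that analysis without contradicting it.

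**Conclusion.** The point holds as a fault in a stated rule. A concern about one factor ends participation in both, which can produce avoidable missing outcomes and lost website exposure, possibly related to drug allocation. It also blurs a drop-out rate that the pilot exists to estimate.

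The size is uncertain. Without a safety-stop rate, neither the magnitude nor the direction of bias can be stated. Power is unchanged if the stops fall within the 20% allowance. The fall to between 78.6% and 73.5% is a sensitivity range that rests on assumed stop rates of 1% to 10%, an unadjusted t-test and a worst case for overlap with other drop-out. It would be wrong to read it as a demonstrated shortfall. The case for changing the rule rests mainly on the missing data and the merged rates, and only secondarily on power. The change is worth making because it is cheap and loses nothing.

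**What to change.** Reword the withdrawal criteria so that a safety concern about the medication ends trial medication only. The participant keeps the allocated website condition, is asked for the 6- and 12-week questionnaires and included in the notes review unless consent to follow-up is withdrawn, and is analysed in the groups to which they were randomised. Keep withdrawal from the trial for invalid consent or the participant's own decision to leave. Report medication discontinuation and loss to follow-up as separate rates, by drug and by website condition.

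The cost is a change of wording and one extra item to record. The questionnaires, reminders, telephone collection and notes review are already planned, and the sample size does not change.
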